### Randomization

A research coordinator will randomize the participants. An independent statistician will generate a list of random numbers. Eligible participants will be randomly assigned at a ratio of 1:1:1 to the flow reduction first (FR) group, the FiO_2_ reduction first (OR) group, or the simultaneous reduction (SR) group, in accordance with the predefined randomization list with a block size of 3. Information about the randomization will not be provided to the research supervisor, co-researcher, or patients. In the case of an emergency, co-researchers who are aware of the random assignments should avoid participating in future results analysis.

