### Types of interventions

After randomization, the participants will undergo FR, OR, or SR strategies for weaning off the HFNC. In the FR group, flow will gradually be reduced by 10 L/min/h. When it reaches 20 L/min, FiO_2_ reduction will then begin at 0.1 /h until it reaches 0.3. In the OR group, FiO_2_ will gradually be reduced by 0.1 /h until it reaches 0.3. At this point, flow will be reduced by 10 L/min/h until it reaches 20 L/min. Finally, in the SR group, both flow and FiO_2_ will be gradually reduced simultaneously at a rate of 10 L/min and 0.1 /h, respectively, until they reach the HFNC weaning-off targets (20 L/min for flow and 0.3 for FiO_2_). Weaning will proceed only when the patient satisfies all the weaning criteria at every weaning point. When flow and FiO_2_ reach weaning-off targets, the patient will be transferred to conventional oxygen therapy, such as low-flow nasal prongs.

We have followed the Standard Protocol Items: Recommendations for Interventional Trials (SPIRIT) 2013 statement, which defines the standard protocol items for clinical trials [18] (see Additional file 1). The study algorithm is depicted in Fig. 1 and the SPIRIT schedule is shown in Fig. 2.

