### Definitions

Weaning success is defined as a condition in which the patient meets all of the weaning criteria after 24 h of conversion to conventional oxygen therapy. A weaning failure is defined as the patients requiring re-application of the HFNC within 24 h of conversion to conventional oxygen therapy or needing NIV or endotracheal intubation during the HFNC weaning period or within 24 h of conversion to conventional oxygen therapy. If clinical improvement is not seen during follow up, NIV or intubation should be considered according to the clinician’s judgment. Immediate endotracheal intubation will be considered when there are two or more of the following conditions according to standard clinical practice: respiratory rate > 40 breaths/min, arterial pH < 7.2, PaO_2_ < 50 mmHg, signs of high work of breathing such as use of accessory muscle, abdominal paradox, need to secure the airway due to increased sputum, or altered mental status.

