## Discussion

The HFNC is usually applied in critically ill patients. We therefore considered a study design that would minimize the risk to the patients. First, we adopted strict criteria for both patient inclusion and the weaning process to ensure patient safety. Second, we decided to compare three stepwise weaning protocols for HFNC without including immediate withdrawal from HFNC. The potential advantage of immediate withdrawal is a considerable shortening of the weaning process. However, risk of failure and the need for reinstitution of the HFNC or intubation is a major concern. In contrast to immediate withdrawal, stepwise weaning may minimize atelectotrauma and gradually increase respiratory muscle strength without the associated risk of atelectasis. Finally, the attending physician and nurse are requested to assess the patient’s condition within 30 min of changing the HFNC setting. In this study, several clinical outcomes will be compared between these three groups. After completion of the study, we hope to be able to suggest the best strategy for the withdrawal of the HFNC in adult patients.

There are several strengths of this study design. This will be the first study to evaluate HFNC weaning strategies in an adult population. It has been designed as a prospective RCT, which is one of the most powerful study designs. Furthermore, we will not conduct any medical tests or interventions other than HFNC weaning in this study in order to reflect the actual clinical situation. There are also some limitations of this study, namely, the small sample size and the fact that the study will be conducted at a tertiary referral hospital. In addition, we will adopt 1-h interval weaning, which is slower than the HFNC weaning process used in clinical practice. However, it was a necessary choice to ensure patient safety. Given the shortcomings of this first study, further additional studies will eventually be required on larger scale.

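### The protocol treats knowing the allocation as an emergency exception, but during weaning the arm can be read from the HFNC settings after the first change

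*Protocol article*

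**What the plan says.** The Randomization section of the protocol article names three parties who are not told the allocation: "Information about the randomization will not be provided to the research supervisor, co-researcher, or patients". The next sentence sets a consequence for those who find out: "In the case of an emergency, co-researchers who are aware of the random assignments should avoid participating in future results analysis".

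Types of interventions defines the arms purely by the order in which two settings fall. For flow first: "In the FR group, flow will gradually be reduced by 10 L/min/h", with FiO2 following once flow is at 20 L/min. For FiO2 first: "In the OR group, FiO_2_ will gradually be reduced by 0.1 /h until it reaches 0.3", with flow following. In the third arm both fall together. Each step is gated: "Weaning will proceed only when the patient satisfies all the weaning criteria at every weaning point".

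The Discussion asks the attending physician and nurse to assess the patient "within 30 min of changing the HFNC setting". The Definitions section starts the failure definition with re-application: "A weaning failure is defined as the patients requiring re-application of the HFNC within 24 h of conversion to conventional oxygen therapy". It adds need for NIV or intubation, and leaves these to the clinician's judgement. Listed conditions exist only for immediate intubation.

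**The concern.** A rule that removes people from the analysis because they know assignments makes sense only if they are meant to stay unaware after allocation. The text therefore describes more than concealment of a list. Yet the intervention is the visible pattern of settings, so for anyone who looks at the device, awareness is routine.

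This matters because some decisions that feed the endpoints are judgements. The step criteria include recovery from the underlying condition and absence of distress signs such as agitation or anxiety. No threshold is given for re-applying HFNC, and starting NIV is discretionary. These decisions enter the primary outcome, time to successful weaning, and the second half of the hypothesis, that failures do not increase. A reader who takes the masking at face value would give the results more credit for unbiased assessment than the design earns.

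**Working it through.** The plan gives no figure on this point. The check is whether the settings reveal the arm, and what follows from that.

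**Inputs.** Targets are 20 L/min and 0.3; steps are 10 L/min and 0.1 per hour (Types of interventions). FiO2 at entry is at most 0.5 (Study design and patients). Starting flow is not given, so 20 to 60 L/min is assumed.

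**Does one change reveal the arm?** Example with an assumed start of 40 L/min and 0.5:

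| Arm | Setting after first change | Scheduled steps to target |
|---|---|---|
| Flow first | 30 L/min, 0.5 | 4 |
| FiO2 first | 40 L/min, 0.4 | 4 |
| Simultaneous | 30 L/min, 0.4 | 2 |

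The full grid has 5 flows (20, 30, 40, 50, 60) × 3 FiO2 values (0.3, 0.4, 0.5) = 15 starting points. Both settings are above target at 4 × 2 = 8 of them, and at all 8 the first change gives three different settings. At the other 7, one setting is already at target and the three sequences are identical. So the arm stays hidden only where the arms do not differ. The 8 of 15 counts grid points, not patients.

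**Who sees the settings?** The attending physician and nurse do, after every change. So does any co-researcher who looks at the device or the hourly record. The article describes no sham setting, hidden display or masked assessor. After conversion to conventional oxygen the settings no longer show the arm, so knowledge at re-application rests on recall or the chart.

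**How much room is there in the time endpoint?** With a = (flow − 20)/10 and b = (FiO2 − 0.3)/0.1, the sequential arms need a + b steps and the simultaneous arm max(a, b). The scheduled saving is a + b − max(a, b) = min(a, b), at most (0.5 − 0.3)/0.1 = 2 h. If a hold lasts one hourly interval (assumed; the article gives no re-check interval), one hold uses at least half of a patient's scheduled saving.

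**How much room is there in the failure endpoint?** With 30 per arm, one event is 1/30 = 3.3 percentage points. Under the paediatric HFNC failure rate of 10.5%, 0.105 × 30 = 3.15 failures are expected per arm, and one event is 1/3.15 = 32% of them. Under the stepwise NIV figure (74% success, hence 26% failure), 0.26 × 30 = 7.8 are expected, and one event is 1/7.8 = 13%. These figures show how coarse the endpoint is. They do not estimate bias.

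**Side consequence.** Allocation is "in accordance with the predefined randomization list with a block size of 3". Someone who sees earlier arms and tracks the blocks guesses right with average probability (1/3 + 1/2 + 1)/3 = 61%, against 33% by chance. Whether anyone enrolling patients is in that position is not stated.

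**The case against.** The strongest reply is that the article never says blind or masked. The sentence stands beside the description of list generation and could mean only that the list is concealed. The attending physician and nurse are not among those from whom information is withheld, and nothing places co-researchers at the bedside. This stands as a limit on who is affected. It does not rescue the second sentence, which only works if unawareness is meant to continue after allocation.

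Three stronger readings are tempting, and the documents do not support them.

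- A reader might infer that the exclusion rule would bar nearly every researcher from the analysis. The article does not say which researchers see patients or settings, so the number cannot be known. For patients the case is also weaker: they may feel a change in flow without knowing their arm.
- A reader might infer that the trial has no protection against assessment bias. It has some. Steps are gated on numeric limits for pH, SpO2 with FiO2, respiratory rate, heart rate and systolic pressure. Success requires all of these criteria after 24 h on conventional oxygen. Vital signs are monitored throughout, and keeping aware co-researchers out of the analysis is itself a safeguard.
- A reader might take one re-application as a third of the failure rate and call that the bias. That fraction depends on a paediatric rate which the article itself considers hard to carry over to adults; under the NIV figure it is about an eighth. Neither says how often judgement would differ by arm.

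Reason fields and sensitivity analyses may sit in a fuller document. Their absence from the article is not the point; the unworkable statement about allocation is.

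**Conclusion.** The point holds in a limited form. The Randomization section gives the trial a property that its interventions cannot deliver to anyone who sees the settings: the arm is known after the first change whenever both settings start above target. Treating awareness as an emergency exception does not fit such a design. Some judgement remains in step progression, HFNC re-application and NIV, exercised by staff who can know the arm, while most step and success criteria are numeric. The direction and size of any bias cannot be derived from the document.

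The conclusion rests on reading the two sentences together as meaning unawareness after allocation, and on starting flows above 20 L/min being usual, which the article does not state. It deserves correction because the statement is wrong for this design and the change is cheap.

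**What to change.** Replace the two sentences in Randomization with a statement on these lines:

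- the trial is open-label to bedside staff and to anyone who sees the HFNC settings or their record;
- the allocation list is concealed until each assignment;
- the analysis is done under coded arm labels by someone who neither generated nor holds the list and did not attend patients. The independent statistician who produces the list should therefore not be assumed to fill this role. The analysis file should not carry the hourly settings, because they would break the code.

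At each hold, HFNC re-application, NIV start or intubation, record the reason and the SpO2, respiratory rate, heart rate and blood pressure that are already monitored, plus pH where a blood gas was taken for usual care.

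Leave the primary failure definition unchanged. Add one prespecified sensitivity analysis that reports, by arm, the holds and failures with and without at least one of the protocol's own recorded numeric criteria unmet. pH will be missing for some events, and FiO2 is not a set value on low-flow prongs, so that criterion cannot be judged after conversion. Events should be tabulated rather than dropped, because a patient back on HFNC has no defined 24 h success status.

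The cost is an openly stated open-label design, one extra form field and one extra analysis. Recruitment began in January 2019, so this is an amendment to the review board and the registry, and the new field will be complete only from its adoption. Clinical decisions are unchanged.

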### Types of interventions

After randomization, the participants will undergo FR, OR, or SR strategies for weaning off the HFNC. In the FR group, flow will gradually be reduced by 10 L/min/h. When it reaches 20 L/min, FiO_2_ reduction will then begin at 0.1 /h until it reaches 0.3. In the OR group, FiO_2_ will gradually be reduced by 0.1 /h until it reaches 0.3. At this point, flow will be reduced by 10 L/min/h until it reaches 20 L/min. Finally, in the SR group, both flow and FiO_2_ will be gradually reduced simultaneously at a rate of 10 L/min and 0.1 /h, respectively, until they reach the HFNC weaning-off targets (20 L/min for flow and 0.3 for FiO_2_). Weaning will proceed only when the patient satisfies all the weaning criteria at every weaning point. When flow and FiO_2_ reach weaning-off targets, the patient will be transferred to conventional oxygen therapy, such as low-flow nasal prongs.

We have followed the Standard Protocol Items: Recommendations for Interventional Trials (SPIRIT) 2013 statement, which defines the standard protocol items for clinical trials [18] (see Additional file 1). The study algorithm is depicted in Fig. 1 and the SPIRIT schedule is shown in Fig. 2.

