### Study design and patients

This study is a prospective, investigator-initiated, randomized controlled study with three experimental groups. Patients aged over 18 years receiving respiratory support through a HFNC for any indication will be screened for study participation. Participants satisfying all weaning criteria, whether they are medical or surgical, will be prospectively recruited after providing written informed consent. The weaning criteria are as follows: patients who have recovered from their underlying condition, show no signs of respiratory distress (such as agitation, diaphoresis, or anxiety), with arterial pH ≥ 7.35, partial pressure of oxygen (SpO_2_) > 90% with FiO_2_ ≤ 0.5, respiratory rate ≤ 25 breaths/min, heart rate ≤ 120 beats/min, and systolic blood pressure (SBP) ≥ 90 mmHg. Patients will be excluded from the study if they have severe hypercapnia (pH < 7.25), respiratory arrest requiring tracheal intubation, cardiac arrest, acute coronary syndrome or life-threatening arrhythmias, or failure of more than two organs. Patients who have had recent trauma or burns to the neck and face, are pregnant, or who refuse to participate or cooperate in the study will be also excluded.

Informed consent will be obtained from the patients when they are ready to be weaned off the HFNC. However, if the patients cannot understand information about the study, remember the information, or communicate their decision by talking, using sign language, or any other means, they will be considered to be unable to make a decision. In that case, consent will be obtained from their families or the legal representatives.

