### Statistical analyses

Statistical analyses will be performed on both a per-protocol (PP) and an intention-to treat (ITT) basis. For the PP analysis, all participants who complete the study will be included to evaluate the primary and secondary outcomes. For the ITT analysis, all participants enrolled and randomized to one of the three groups will be included. In the interim analysis, if the *P* value is < 0.003, we will stop the study early, accepting the significance of the outcome. If not, we will recruit the remaining half of the subjects. Sub-group analysis according to the respiratory failure type (hypoxemic or hypercapnic) is planned. Unless otherwise specified, continuous variables will be expressed as mean plus standard deviations or median and categorical variables as percentages. Student’s *t* test will be used to compare continuous variables; the chi-square or Fisher’s exact test will be used to compare categorical variables. Unless otherwise stated, all tests are two-sided and performed at the 0.05 significance level. Analyses will be performed using SPSS 20.0 (IBM Corp., Armonk, NY, USA).

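### Starting flow and FiO2 set each patient's minimum weaning time, but the stated t test and the allocation ignore them, so precision is lost

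*Protocol article*

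**What the plan says.** The protocol article's section on types of interventions fixes the schedule.

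- Flow-first arm (FR): "In the FR group, flow will gradually be reduced by 10 L/min/h"; once flow is at 20 L/min, FiO2 falls by 0.1 per hour to 0.3.
- FiO2-first arm (OR): FiO2 goes to 0.3 first. Then, "At this point, flow will be reduced by 10 L/min/h until it reaches 20 L/min".
- Simultaneous arm (SR): "both flow and FiO_2_ will be gradually reduced simultaneously at a rate of 10 L/min and 0.1 /h, respectively". The two settings keep moving in this way "until they reach the HFNC weaning-off targets".

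A step is taken only if the weaning criteria are met at that check.

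Under study design and patients, anyone "receiving respiratory support through a HFNC for any indication will be screened for study participation". The weaning criteria include "partial pressure of oxygen (SpO_2_) > 90% with FiO_2_ ≤ 0.5", which caps starting FiO2. No lower limit on starting flow or FiO2 is listed. The randomisation section uses 1:1:1 allocation in blocks of 3 and names no stratification factor. Under statistical analyses, Student's t "test will be used to compare continuous variables". The only baseline factor mentioned there is a subgroup analysis by type of respiratory failure. The primary outcome is time to successful weaning.

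**The concern.** The shortest possible weaning time is fixed by two numbers known before randomisation, and they differ between patients by several hours. An analysis that ignores them leaves that spread in the error term. The scheduled advantage of the simultaneous arm is itself only 0, 1 or 2 hours, so the spread is not small beside the effect. Patients with nothing left to reduce on one axis follow the same steps in every arm and pull the average difference towards zero.

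The trial has little precision to spare. The 30 per arm is taken by precedent, without an effect size, SD or power, and the Discussion names small sample size as a limitation.

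**Working it through.** **The plan's own figure.** 90 / (1 − 0.10) = 100, which matches the stated total. No power figure is given, so none can be reproduced. With 30 v 30 at two-sided 0.05, 80% power needs a standardised difference of (1.960 + 0.842) × √(2/30) = 0.72.

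**Minimum times from the protocol's rules.** Let a = (flow − 20)/10 and b = (FiO2 − 0.3)/0.1. An uninterrupted course takes a + b hours in FR and OR and max(a, b) hours in SR. The saving is min(a, b). Since FiO2 ≤ 0.5, b ≤ 2 and the saving is at most 2 h.

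| Start (L/min, FiO2) | FR = OR (h) | SR (h) | Saving (h) |
|---|---|---|---|
| 60, 0.5 | 6 | 4 | 2 |
| 40, 0.5 | 4 | 2 | 2 |
| 40, 0.4 | 3 | 2 | 1 |
| 30, 0.4 | 2 | 1 | 1 |
| 60, 0.3 | 4 | 4 | 0 |
| 20, 0.5 | 2 | 2 | 0 |

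**Dilution (baseline mixes are assumptions).**

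- Flow 30–60 L/min and FiO2 0.3, 0.4 or 0.5, evenly spread: one third start at FiO2 0.3. The mean saving is (0 + 1 + 1.75)/3 = 0.92 h overall and (1 + 1.75)/2 = 1.38 h in the rest.
- Flow 20–60 L/min, same FiO2 values: 7 of 15 combinations (47%) have zero saving. The mean is 11/15 = 0.73 h overall and 11/8 = 1.38 h in the rest. Starting settings alone then give an SD of 1.63 h in the sequential arms and 1.18 h in SR.
- Over the mixes tried, the zero-saving share ran from 10% to 55%.

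**Gain from adjustment.** These are simulations of SR v FR, 30 per arm, comparing a t test with a linear model on arm, a and b. A hold is an hourly check at which no step is taken. The first two groups use the 30–60 L/min mix.

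Short holds (1 h), same pass probability for all patients:

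- 10% holds: variance cut 73%, power 72% to >99%
- 25% holds: variance cut 58%, power 64% to 95%
- 50% holds: variance cut 42%, power 52% to 77%

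Same mix, about 25% holds, one assumption changed at a time:

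- pass probability varying by patient, Beta(3, 1): variance cut 21%, power 37% to 49%
- pass probability more spread, Beta(1.5, 0.5): variance cut 6%, power 22% to 25%
- holds of 4 h: variance cut 23%, power 32% to 40%
- holds of 8 h: variance cut 15%, power 23% to 26%
- added noise SD of 1, 2 or 4 h: power 53% to 81%, 37% to 47%, 18% to 20%

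The 20–60 L/min mix, with the minimum times plus normal residual error:

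- residual SD of 1, 2 or 4 h: power 37% to 72%, 21% to 26%, 10% to 12%

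With a narrow baseline (flow 40–50 L/min, 10% at FiO2 0.3, 1 h holds at 25%), power is already 99% without adjustment.

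**The case against.** Four points can be made on the other side.

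1. *Starting settings fix only the minimum.* A reader might infer that they drive most of the outcome variance. The documents do not show this. Steps wait on the weaning criteria, patients can fail, and no SD is given. Under long or patient-specific holds, the variance explained is modest. This objection stands and governs how the size must be stated.

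2. *The unadjusted comparison is valid.* A reader might infer bias from chance imbalance in starting settings. Randomisation rules that out: such imbalance is sampling error that the t test already allows for. This stands; the loss is one of efficiency.

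3. *The t test is named for continuous variables in general, and an unseen analysis plan could add covariates.* This stands in part. The article is not silent, however: it names a test, that test is unadjusted, and no use of starting settings appears in allocation or analysis.

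4. *Patients with no scheduled contrast may belong in the trial.* A reader might infer that they should be barred from entry. The trial recruits for any indication, and its Discussion says it wants to reflect actual practice, so an average effect over everyone ready to wean is a legitimate target. Narrowing entry would change that target in a trial recruiting since January 2019. The study algorithm figure is also not available here. This stands, so no change to entry is proposed.

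**Conclusion.** The point holds as a matter of efficiency. It follows by arithmetic from the protocol's rules that minimum time is a + b hours in the sequential arms and max(a, b) in SR, that the scheduled saving is at most 2 h, and that it is zero for some patients whom the listed criteria admit. The stated test and the allocation use none of this, so precision is lost. Validity is not affected.

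The direction is clear and the size is not. It depends on the mix of starting settings, the length of holds and how far they vary between patients, none of which the documents supply. The variance reduction ranges from roughly 40–70% under short, similar holds down to about 5–30% under the less favourable assumptions. The change is worth making because it is nearly free, even if the gain proves small.

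**What to change.** - Include starting flow and starting FiO2 at randomisation as covariates in the primary analysis. If a time-to-event analysis is used, stratify it by the planned number of steps.
- Pre-specify a sensitivity analysis in patients with at least one flow step and one FiO2 step outstanding at randomisation. The group is defined by baseline values alone, so the randomised comparison within it is preserved. It will be smaller: 30 × 2/3 = 20 per arm under the 30–60 L/min mix, or 30 × 8/15 = 16 under the 20–60 L/min mix.
- Write both into the analysis plan before any comparison by arm, including the planned interim analysis.

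**Cost.** No new data are needed, since both settings must be known to deliver the intervention. The linear model spends two degrees of freedom and still estimates the average difference in time. Where residual noise was large, its power was at worst about one percentage point below the t test (25% v 24%). A stratified time-to-event analysis estimates a different quantity, so the choice should be stated in advance.
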